## Abstract

**Background:**

Endothelial dysfunction is a hallmark of diabetes mellitus and systemic arterial hypertension (SAH) and an early maker for atherosclerosis. Aerobic exercise training is known to enhance endothelial function, but little is understood about the effects of resistance or combined exercise training on endothelial function. The aim of this study is to investigate the effect of a 12-week aerobic (AT), resistance (RT), or combined (aerobic and resistance, CT) training program on endothelial function and assess associated effects on blood pressure in individuals with SAH.

**Methods/design:**

Eighty-one subjects with SAH aged 18 to 70 years will be selected and randomly assigned to three types of exercise training: AT, RT or CT. The study will involve the following procedures and tests: anamnesis, anthropometric assessment, echocardiography, blood pressure measurements through ambulatory blood pressure monitoring, flow-mediated dilation, ergospirometry, one repetition maximum test (1-RM), and blood collection (number of circulating endothelial progenitor cells, number of circulating endothelial microparticles, lipid profile, glucose, glycated hemoglobin, and creatinine). The AT intervention will consist of a 40-min exercise session with progressive intensities ranging from 50 to 75 % of heart rate reserve. The RT intervention will consist of a 40-minute session with four sets of six to 12 repetitions with a rest period of 60 to 90 seconds between each set and each type of exercise. Weight loads will be adjusted to 60 to 80 % of 1-RM for six types of exercise. The CT intervention will consist of a 20-min aerobic exercise session, followed by an additional 20-min resistance exercise session; each resistance exercise will have two sets less to match the total training volume.

**Discussion:**

The study results are expected evidence of cardiovascular protective effects of different types of exercise training through the modulation of endothelial function in hypertensive individuals. Knowing the magnitude of improvement of endothelium-dependent vasodilation for the different types of exercise training can provide scientific evidence for the prescription of exercise programs for vascular protection targeting hypertensive individuals.

**Trial registration:**

The Brazilian Clinical Trials Registry (http://www.ensaiosclinicos.gov.br/) under RBR-9ygmdn and dated 1 March 2015.

## Background

Cardiovascular diseases are largely determined by multifactorial risk factors that tend to interact and may be present over the course of an individual’s lifetime. Obesity [1, 2], physical inactivity [3, 4], and insulin resistance [5] are all risk factors closely associated with systemic arterial hypertension (SAH) and diabetes mellitus type 2. In addition to these risk factors, smoking [6] and excess weight [7] contribute to endothelial dysfunction [8, 9], which is a hallmark of diabetes mellitus [10] and SAH [11] and an early maker for atherosclerosis [12].

The endothelium is a single layer of cells that lines the tunica intima of blood vessels [13] and plays a major role in the modulation of vascular angiogenesis, inflammatory responses, and vascular tone and permeability [14]. Vascular protection is particularly attributable to endothelial nitric oxide synthase (eNOS), an enzyme involved in the production of nitric oxide (NO).

The balance between endothelial injury and recovery is critical to continuously maintaining endothelial function [15]. The bone marrow releases a progenitor cell subtype called endothelial progenitor cells (EPCs), which have the ability to migrate to the peripheral circulation and differentiate into mature endothelial cells to maintain vascular integrity [16]. EPC levels have been associated with cardiovascular risk factors [17], endothelium-dependent vasodilation [18], and clinical outcomes, including hospitalization and cardiovascular death rates [19]. In patients with cardiovascular risk factors such as SAH [20], smoking [21], metabolic syndrome [22] and diabetes mellitus [23], circulating levels of EPCs can be reduced compared with healthy individuals of matching age and sex. Endothelial dysfunction has been associated with a decreased number and impaired function of EPCs in patients with SAH, diabetes mellitus, and metabolic syndrome, and thus an increased risk of atherosclerosis would be expected [24].

On the other hand, regular exercise, also known as exercise training, produces effects on the cardiovascular system and has been proven to restore endothelial function even in the presence of cardiovascular disease [25]. Regular exercise promotes changes in cholesterol levels and its subfractions; accelerates the removal of chylomicrons and low-density lipoproteins from circulation; increases the release of NO that seems to generate increased expression of eNOS [26]; increases the number of circulating EPCs in healthy individuals [27], as well as in individuals with established cardiovascular disease [28]; and improves plasma glucose [29], which has a direct link to impaired endothelial function [30]. This assumption is consistent with findings in healthy individuals [31], individuals with diabetes mellitus type 2 [32], and patients with cardiovascular conditions [33], showing that exercise training improved vascular function and overall health.

Evidence with clinical relevance exists on the impact of aerobic exercise on BP and blood glucose levels, but no consensus exists regarding the effects of resistance training and even less evidence is available on combined training (resistance and aerobic) and the regulatory mechanisms of endothelial function and its relationship with BP in hypertensive individuals. Thus, despite present evidence showing the benefits of exercise and physical training on blood pressure [34] and blood glucose levels [35], more studies are needed to investigate further the mechanisms involved with endothelial function especially their relationship with blood pressure reduction.

The objective of this study is to evaluate the chronic effects of exercise training on endothelial function modulation in hypertensive patients undergoing a 12-week exercise intervention of aerobic, resistance, or combined (aerobic and resistance) training. Modulation of endothelial function will be assessed by flow-mediated dilation (FMD) [36] and biochemical [37] and cellular parameters [38, 39]. The primary and secondary study objectives are listed in Tables 1 and 2, respectively.

**Table 1 Tab1:** Primary objectives of the study

• To investigate the effects of AT, RT and CT on flow-mediated vasodilation of the brachial artery in hypertensive individuals • To assess the impact of different types of training (AT, RT, and CT) on the number of circulating endothelial progenitor cells and number of circulating endothelial microparticles in hypertensive individuals	

AT, aerobic training; RT, resistance training; CT, concurrent training

**Table 2 Tab2:** Secondary objectives of the study

To assess the effectiveness of different types of training (AT, RT and CT) regarding the following:	
• Blood pressure levels: clinical assessment and ABPM • Serum levels of total cholesterol, HDL, LDL and triglycerides • Fasting blood glucose and glycated hemoglobin • Blood viscosity, RBC deformability, RBC aggregation, fibrinogen levels and ESR • Echocardiography for determination of heart chamber sizes and wall thickness • Functional capacity through maximum oxygen consumption (VO_2_max) • 1-RM • Abdominal obesity and BMI	

ABPM, ambulatory blood pressure monitoring; AT, aerobic training; RT, resistance training; CT, concurrent training; HDL, high-density cholesterol; LDL, low-density cholesterol; RBC red blood cell; ESR, erythrocyte sedimentation rate; 1-RM, one-repetition maximum strength test; BMI, body mass index.

## Methods/design

The study will be coordinated at the Fundação Universitária de Cardiologia (FUC) Health Sciences Graduate Program together with the Instituto de Cardiologia (IC) in the city of Porto Alegre, Rio Grande do Sul, Brazil.

### Study design

A randomized controlled and evaluator-blinded clinical trial will be conducted as shown in Fig. 1.

**Fig. 1 Fig1:**
[figure not shown]
Study design. Flow chart of how the clinical trial will be conducted

### Sample selection

The study sample will comprise individuals with no history of cardiovascular disease (except for SAH controlled with the use of medications), neuromuscular, endocrine, and/or metabolic conditions (except for diabetes mellitus type 2) who are attending the IC health care facilities.

Subjects will be selected based on information collected from their medical records. Eligible individuals will be contacted by telephone and informed of the purpose and procedures of the study. For those willing to participate, a first visit will be scheduled when a clinical questionnaire will be administered, and they will be asked to sign a free informed consent form to participate in the study. Other study visits will be scheduled for those meeting the inclusion criteria of the study (Table 3).

**Table 3 Tab3:** Inclusion and exclusion criteria for the study

Inclusion criteria	Exclusion criteria
• Males and females aged 18 to 70 years • Diagnosed with SAH • Signed a free informed consent form • Considered insufficiently active (IPAQ) • Non-active smokers	• Currently engaging in any type of systematic physical activity • Blood pressure hyper-reactivity in the clinical assessment (SBP > 220 mmHg and/or increase in DBP > 15 mmHg) • Ongoing infectious diseases • Obesity class II or III (BMI) • Heart failure class III or IV; recent cardiovascular event (in the last three months); chronic renal failure; and malignant disease with life expectancy < 2 years • Orthopedic impairments or any physical or mental limitations that prevent physical exercises • After the training intervention, individuals who attended < 85 % or missed > 2 consecutive training sessions will be excluded from the sample. Subjects will be encouraged to complete any missed session at the end of training by performing additional sessions.

SAH, systemic arterial hypertension; IPAQ, International Physical Activity Questionnaire; SBP, systolic blood pressure; DBP, diastolic blood pressure; BMI, body mass index

The following formula will be used for the calculation of sample size (n_p_) to estimate the number of hypertensive individuals to be included in the study:$$ \left({\upmu}_{\mathrm{p}}\right):\ {\mathrm{n}}_{\mathrm{p}0} = {\mathrm{s}}^2/\ {\left({\upmu}_{\mathrm{p}}\hbox{-}\ {\mathrm{x}}_{\mathrm{p}}\right)}^2\mathrm{x}\ {\left({\mathrm{t}}_{\upalpha; \mathrm{g}\mathrm{l}}\right)}^2, $$

where, n_po_ = sample size at time point zero, s^2^ = variance of the sampling distribution, and t_α;gl_ = sampling distribution according to a predetermined error probability (*P* ≤ 0.05) and degrees of freedom for n_po_.

The mean incidence rate of SAH in Brazil is 20 % of the population [40]. Considering the baseline value (n_0_ = 30); t_α;gl_ = t_0.05;29_ = 2.045; s^2^ = 0.05 (based on the maximum value of the coefficient of variation of endothelial vasodilation); and the maximum error of the estimate taken as the maximum variability in arterial diameter measures by two observers (0.02 %) [41], it was estimated that n_p1_ = 26.1 ≅ 26 hypertensive individuals. Thus, in the estimate of *n,* the approximation used considered n_p1_ = 26, gl = 23, and t_0.05;23_ = 2.069. The n_p1_ = 26.8 ≅ 27. The estimate of the sample size for the study was *n* = 80.3 ≅ 81 hypertensive individuals who will be randomly assigned to the three training interventions.

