### Intervention protocols

The study intervention will comprise 12 weeks of exercise sessions, lasting on average 50 min, three times a week. Exercise sessions will include a warm-up period of 5 to 10 min at the beginning, resistance or combined aerobic exercises for 40 min, and a cool down/relaxation period.

AT will be performed on a cycle ergometer for the entire intervention. Subjects will be monitored with heart rate monitors (Table 4).

**Table 4 Tab4:** Intensity and duration of aerobic training on a stationary bike during a 12-week intervention

	Phase I	Phase II	Phase III
Intensity	50 to 65 % HRR	55 to 70 % HRR	60 to 75 % HRR
Session duration	40 min	40 min	40 min
Exercise duration (weeks)	4	4	4

HRR, heart rate reserve

RT will include six types of exercises that alternate between large and small muscle groups (leg press, bench press, knee extension, biceps curl, knee bend, and low row) for the entire training intervention (Table 5).

**Table 5 Tab5:** Intensity, number of sets, repetitions, rest period between sets, and session duration of resistance training during a 12-week intervention

	Phase I	Phase II	Phase III
Intensity	60 % 1-RM	70 % 1-RM	80 % 1-RM
Sets	4	4	4
Repetitions	10 to 12	8 to 10	6 to 8
Rest period between sets	60 s	60 s	90 s
Session duration	40 min	40 min	40 min
Exercise duration (weeks)	4	4	4

1-RM, one-repetition maximum strength test

CT will consist of resistance and aerobic exercises combined in one session performed over a 40-min period set as in the other two protocols, so that training volume is similar across all intervention groups for the entire intervention (Table 6).

**Table 6 Tab6:** Intensity, number of sets, repetitions, rest period between sets, and session duration of concurrent training during a 12-week intervention

	Phase I	Phase II	Phase III
Resistance training			
Intensity	60 % 1-RM	70 % 1-RM	80 % 1-RM
Sets	2	2	2
Repetitions	10 to 12	8 to 10	6 to 8
Rest period between sets	60 s	60 s	90 s
Session duration	20 min	20 min	20 min
Aerobic training			
Intensity	50 to 65 % HRR	55 to 70 % HRR	60 to 75 % HRR
Session duration	20 min	20 min	20 min
Exercise duration (weeks)	4	4	4

1-RM, one-repetition maximum strength test; HRR, heart rate reserve

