A basic training principle is the progression of exercise intensity, duration, or frequency. Progression of exercise in the study intervention will be through gradual exertion increase for the protocols [46]. Borg’s rating scale of perceived exertion (6 to 20 point scale) will be used to help control the training intensities [47]. All subjects will be allowed an initial adjustment period. Those with resting BP levels higher than 160 mmHg (SBP) and/or 105 mmHg (DBP) before cardiopulmonary testing, 1-RM, or an exercise session (AT, RT and CT) will not be allowed to participate in any activities [40]. Those experiencing BP higher than the recommended level on a second occasion will be referred to the study cardiologist for evaluation. The cardiologist will determine whether the subject can continue participating in the study.

Subjects diagnosed with SAH and diabetes mellitus type 2 will have their blood glucose checked (Optium Xceed, Abbott Diabetes Care, Inc., Alameda, CA, USA) in addition to BP measurements before cardiopulmonary exercise testing, 1-RM or an exercise session (AT, RT, and CT) and every 15 min throughout exercise sessions. If the blood glucose levels are lower than 100 mg/dL during cardiopulmonary exercise testing, 1-RM, or exercise sessions (AT, RT and CT), subjects will receive 30 to 45 g glucose gel (Gli-Instan, Lightsweet ™) to maintain levels above 120 mg/dL, and their blood glucose will be checked again 15 min later. Those with blood glucose higher than 250 mg/dL will have their urine tested for the presence of ketones (ComboStik™, Gyung-Nam, Korea), and they will be allowed to resume exercise only if test results are negative. Subjects with blood glucose lower than 100 mg/dL during exercise sessions will have to discontinue exercising and be offered a snack. Their blood glucose will be tested again 15 min later, and they will be allowed to resume exercise only if their test results are acceptable [48].

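### Table 3 removes randomised subjects from the sample after training for low attendance, so the arm comparison is no longer protected by randomisation

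*Protocol article*

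**What the plan says.** The rule is the last exclusion criterion in Table 3 (Sample selection). It begins "After the training intervention, individuals who attended", sets a limit of 85 %, and adds that those who missed more than two "consecutive training sessions will be excluded from the sample". The same bullet continues: "Subjects will be encouraged to complete any missed session at the end of training by performing additional sessions".

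The number of sessions follows from Intervention protocols: "The study intervention will comprise 12 weeks of exercise sessions, lasting on average 50 min, three times a week". Randomization procedure allocates up to 27 subjects to each of three arms, with allocation disclosed after the baseline assessment, so training and attendance come after randomisation.

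Intervention protocols also states that subjects whose resting blood pressure is above 160 mmHg systolic and/or 105 mmHg diastolic before a test or session "will not be allowed to participate in any activities". On a second occasion they go to the study cardiologist: "The cardiologist will determine whether the subject can continue participating in the study". Blood pressure is a secondary objective in Table 2: "Blood pressure levels: clinical assessment and ABPM".

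Statistical procedures lists tests and a significance level. It does not modify the Table 3 rule.

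**The concern.** An exclusion criterion normally acts before allocation. This one acts on what subjects did under the programme to which they were allocated, and its consequence is removal from the sample rather than membership of a secondary analysis set.

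Randomisation makes the three groups comparable as allocated. It does not make the subgroups who keep up with cycling, with resistance work, or with both comparable. If tolerance, injury or motivation affects attendance and is also related to the vascular response, the retained groups can differ for reasons other than the training effect. This touches the primary comparisons: FMD, endothelial progenitor cells and microparticles.

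A second, smaller problem is that the rule cannot be applied uniformly as written, because the article does not define a missed session. Whether a subject stays in the sample could then be settled case by case, after allocation is known.

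**Working it through.** **The threshold in sessions.** 12 weeks x 3 = 36 sessions. 0.85 x 36 = 30.6, so at least 31 must be attended: 31/36 = 86.1 % passes and 30/36 = 83.3 % fails. A sixth miss that is not made up therefore excludes. More than two consecutive misses means three in a row, which is one training week. A subject with only those three misses attended 33/36 = 91.7 %, well above 85 %, and is still removed.

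**How many subjects the rule could remove.** The article gives no expected attendance or exclusion rate, so there is no figure of its own to reproduce. I assume that each session is missed independently with probability p. Let f_k(m, r) be the probability that, after k sessions, a subject is still in the sample with m misses in total and a current run of r misses:

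- session attended: f_{k+1}(m, 0) = (1 − p) x sum over r of f_k(m, r)
- session missed: f_{k+1}(m+1, r+1) = p x f_k(m, r), allowed only if m+1 ≤ 5 and r+1 ≤ 2
- probability of exclusion = 1 − sum of f_36(m, r)

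The first reading applies both limits (no make-ups). The second drops the limit on m: make-ups restore the total, but a run of three still excludes.

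| Assumed miss rate p | Excluded, no make-ups | Expected number of 81 | Excluded, consecutive rule only | Expected number of 81 |
|---|---|---|---|---|
| 5 % | 1.15 % | 0.9 | 0.40 % | 0.3 |
| 8 % | 7.25 % | 5.9 | 1.60 % | 1.3 |
| 10 % | 15.66 % | 12.7 | 3.03 % | 2.5 |
| 15 % | 47.13 % | 38.2 | 9.43 % | 7.6 |

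At p of 10 % or 15 % the two readings differ by a factor of about five (15.66/3.03 = 5.2; 47.13/9.43 = 5.0), so how make-ups count matters a great deal. A third reading, in which a made-up session also cancels a run, would exclude only those who do not make sessions up. Absences from illness or travel tend to cluster, which would change both columns.

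**Bias.** If the mean difference between excluded and retained subjects is the same in both arms, the bias in an arm contrast is (difference in excluded fraction) x (that mean difference). The document supplies neither factor. Equal exclusion rates would not guarantee zero bias either, because different kinds of subject may drop out of different programmes.

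**Blood pressure.** Table 3 counts missed sessions. Intervention protocols bars subjects with high readings from sessions. Neither says whether a barred session is a missed one. If it is, exclusion could be related to blood pressure; if not, this route closes.

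**The case against.** The strongest defence is that analysis sets are usually left to a statistical analysis plan or full protocol, neither of which is shown. That is right as far as it goes: the lack of a statement that all randomised subjects are analysed is not a fault in itself. But the article goes further and fixes their removal, so a plan that analysed everyone would contradict it.

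Make-up sessions also soften the rule. This stands, and it is why the no-make-up column cannot be read as a forecast.

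A reader might infer three stronger points that the document does not support.

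- *That uncontrolled blood pressure leads to exclusion, so the blood pressure result is selected on blood pressure.* The article never says that a barred session counts as missed. Repeat high readings have their own route to the cardiologist, which for bars in a row comes before a third miss. Sample selection describes the hypertension as controlled with medication, so repeated bars may be uncommon.
- *That a bias can be quoted.* Assuming 20 % versus 5 % excluded and a response 2 to 4 percentage points lower in those excluded gives 0.15 x 2 = 0.3 to 0.15 x 4 = 0.6 points, but every input is invented. Nor can this be set against the sample-size section's maximum error, which is printed as 0.02 % and described as observer variability in arterial diameter, not as a difference in FMD.
- *That exclusions will differ between arms.* The arms share frequency, duration and session length, and nothing shown indicates different attendance. It is a possibility that the design should not be exposed to.

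**Conclusion.** The concern holds for the exclusion rule itself. Followed as written, it removes randomised subjects for post-randomisation behaviour that the assigned programme can affect, and the comparisons of FMD and cell counts lose the protection of randomisation. This conclusion needs no numerical assumption.

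The extent is uncertain: about 1 to 47 % excluded without make-ups and about 0.4 to 9 % if make-ups restore the total, under assumed independent miss rates of 5 to 15 %. The direction and size of the bias are unknown. If attendance were unrelated to outcome in every arm there would be no bias, only a loss of precision.

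The link to blood pressure is conditional. It arises only if barred sessions count as missed, and it concerns a secondary outcome most directly.

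**What to change.** 1. Delete the attendance bullet from the exclusion criteria in Table 3.
2. State that the primary analysis includes every randomised subject in the assigned arm.
3. Call all subjects for the post-training FMD, blood and ambulatory blood pressure assessments, whatever their attendance.
4. Keep the attendance rule only to define a supplementary per-protocol set.
5. For that set, reconcile Table 3 with Intervention protocols: say how sessions barred for high blood pressure and sessions made up later count, both towards the 85 % and towards the consecutive rule. No clinical threshold needs to change.

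The cost is a wording change and the recall of low attenders for assessments already planned. Some will not return, so the analysis must say how missing post-training outcomes are handled. The effect estimate may be somewhat diluted compared with one in adherers. The article gives the trial status as recruiting, so the change helps most if made now; subjects already excluded may not be recoverable.

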### Assessment of flow-mediated dilation (FMD)

Endothelial function will be measured noninvasively by using brachial artery ultrasound (EnVisor series, Philips Ultrasound, Bothell, WA, USA). This assessment will be performed with a 7 to 12 MHz linear transducer in a heated room at 21 to 24 °C at ICFUC. A software program will be used for two-dimensional color-Doppler imaging acquisition with a simultaneously recorded electrocardiogram (ECG). Image data will be recorded on a DVD. To minimize operational errors, the subject’s arm, and the ultrasound transducer will be positioned and maintained in the same position during the procedure. Baseline images will be recorded. A cuff will be placed around the forearm and inflated to 50 mmHg above systolic pressure for at least 5 min and then removed. Longitudinal ultrasound images of the brachial artery walls will be acquired to assess endothelium-dependent vasodilation. The expected coefficient of variation between the images will be 1.8 to 5.0 %. Flow-dependent vasodilation responses will be expressed as the percentage change in the brachial diameter [36].

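### The sample size of 81 does not follow from its printed inputs, and the single-mean formula behind it states no power or precision for the comparison of the three arms.

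*Protocol article*

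**What the plan says.** All of the calculation is in the protocol article, under Sample selection. The formula is n = s²/(μ − x)² × t², with "s^2^ = variance of the sampling distribution".

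- **Variance term.** s² is set to "0.05 (based on the maximum value of the coefficient of variation of endothelial vasodilation").
- **Error term.** It is the "maximum error of the estimate taken as the maximum variability in arterial diameter measures by two observers", printed as 0.02 % and attributed to a cited source.
- **First pass.** A starting n of 30 with "t_0.05;29_ = 2.045" gives 26.1.
- **Second pass.** With n = 26, "gl = 23, and t_0.05;23_ = 2.069", it gives 26.8, rounded to 27.
- **Total.** 80.3, rounded to 81 and divided among three arms.

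The section on flow-mediated dilation (FMD) says: "The expected coefficient of variation between the images will be 1.8 to 5.0" %. Randomization procedure assigns 27 subjects to each of aerobic (AT), resistance (RT) and combined (CT) training. Statistical procedures plans comparisons across groups at 0.05. Ethical issues makes an offer of AT after the study depend on how RT and CT fare against AT.

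**The concern.** There are two separate problems. First, a reader who puts the printed inputs into the printed formula does not get the printed answer, so the only justification given for 81 cannot be checked as it stands.

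Second, the formula answers a different question from the one the trial will analyse. It asks how many subjects are needed to estimate one mean within a stated margin. It has no between-arm difference and no power term. Its two inputs are described as a coefficient of variation and an observer error, not as the between-subject spread of the FMD response and a difference worth detecting. Tripling the answer gives three single-mean estimates, not a sized comparison.

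At stake is how the AT/RT/CT results will be read. Without a stated precision for the contrast, readers cannot tell what size of difference the trial could have missed.

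**Working it through.** **Inputs (Sample selection):** s² = 0.05; error = 0.02 %; t = 2.045 (29 df), then 2.069 (23 df). Both t values are correct two-sided 5 % points for the df shown.

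**1. Reproducing the printed figures: n = s²/error² × t²**

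| Reading | First pass (t = 2.045) | Second pass (t = 2.069) |
|---|---|---|
| s² = 0.05, error 0.0002 (0.02 % taken literally) | about 5.2 million | about 5.4 million |
| s² = 0.05, error 0.02 | 0.05/0.0004 × 4.182 = 522.8 | 535.1 |
| s = 0.05 (s² = 0.0025), error 0.0002 | about 261,000 | about 268,000 |
| s = 0.05 (s² = 0.0025), error 0.02 | 6.25 × 4.182 = 26.14 | 6.25 × 4.281 = 26.75 |

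Only the last row matches the printed 26.1 and 26.8. Its total, 3 × 26.75 = 80.26, matches the printed 80.3. Two labels therefore disagree with the calculation actually done: s² where s was used, and a percent sign on 0.02. The first alone changes n by a factor of 0.05/0.0025 = 20.

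**2. Degrees of freedom.** The first pass uses n − 1 (30 gives 29). By the same rule the second pass, with n = 26, should use 25. Then t = 2.060 and n = 6.25 × 2.060² = 26.5, which still rounds to 27.

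**3. What the formula controls.** Rearranged, error = t × s/√n, which is the 95 % confidence half-width of one mean. For a difference between two arms with a common SD the half-width is t × SD × √(2/n). With n = 27 per arm, √(2/27) = 0.272; with t = 2.007 (52 df) the half-width is 0.55 SD. The article gives no SD for FMD or its change.

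**4. What 27 per arm gives for a pairwise contrast.** Two-sided tests, every randomized subject analysed. The standardized differences d (difference/SD) are assumptions.

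| Assumed d | Power, α = 0.05 | Power, α = 0.05/3 |
|---|---|---|
| 0.3 | 20 % | 10 % |
| 0.5 | 45 % | 29 % |
| 0.8 | 84 % | 71 % |

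The table uses the normal approximation; the noncentral t gives slightly less (44 % at d = 0.5, α = 0.05).

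Difference detectable with 80 % power:
- normal approximation: (1.960 + 0.842) × 0.272 = 0.76 SD;
- noncentral t: 0.78 SD;
- with Bonferroni for three pairs: about 0.9 SD (0.88 normal, 0.91 noncentral t).

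**5. In FMD units.** For an assumed SD of 2 to 6 percentage points, the unadjusted detectable difference runs from 0.78 × 2 = 1.6 to 0.78 × 6 = 4.7 percentage points.

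**The case against.** Several points on the other side stand.

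- **The n was computed consistently.** One reading of the inputs returns every printed figure, so this is mislabelling rather than a failed calculation. It would be wrong to infer that the trial really needs 523 or millions per group; those values only show that the text does not match its own result.
- **The df slip is immaterial,** since 27 per arm is unchanged.
- **Precision per arm is a legitimate aim.** Table 1 speaks of investigating effects, and the Discussion stresses the magnitude of improvement. But Statistical procedures and Ethical issues also plan comparisons between arms, and the calculation gives nothing for those.
- **The origin of 0.05 is not certain.** Sample selection calls it a coefficient of variation of vasodilation; the FMD section gives an image-to-image coefficient with the same 5.0 % upper end. The link is probable but not stated.

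Three stronger readings are tempting but unsupported. A reader might say that 81 carries no power; it has power, but none is stated or derivable from this formula. A reader might take 5 percentage points as the SD and 2 as the target difference and report about 30 % power. The article offers neither figure in that role, and using measurement-error inputs that way repeats the fault being criticised. Finally, a reader might declare s = 0.05 and error = 0.02 to be the correct inputs. They are back-solved from the answer, and the source of the error value is not available here.

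**Conclusion.** The point holds. As printed, the inputs do not yield 26.1: with error 0.02 they give about 523, twenty times as many. The calculation is recoverable only by reading 0.05 as a standard deviation and dropping the percent sign.

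The method also fails to support the planned comparison, because it is a one-mean precision target multiplied by three. Under a two-sided 0.05 level with 27 analysed per arm, 80 % pairwise power is reached only from about 0.76 to 0.78 SD, or about 0.9 SD with Bonferroni. No SD or between-arm difference comes from the article, so every power figure here rests on assumption. The analysed number may also be below 27, since Table 3 removes low attenders after training and the calculation has no allowance for this.

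None of this shows that 81 is too few. It shows that the article does not say what 81 is enough for.

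**What to change.** Keep 81 and rewrite the sample-size paragraph:

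1. State the quantity, unit and source of both inputs, and reconcile s with s² and 0.02 with 0.02 %. The authors must settle this from their own source.
2. Use 25 degrees of freedom in the second pass, or explain 23.
3. Say that 27 per arm was derived as a precision target for a single mean.
4. Add what 27 per arm gives for the between-arm FMD contrast: the confidence half-width, the difference detectable with 80 % power (about 0.76 to 0.78 SD unadjusted, about 0.9 SD with Bonferroni for three pairs) and the power at a moderate difference (about 45 % at 0.5 SD). If FMD units are used, show a range such as 1.6 to 4.7 percentage points for SDs of 2 to 6, and label every SD and difference as an assumption.

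The cost is one paragraph. No subjects are added and no procedure changes. The drawback is that the stated justification will look weaker than it does now.
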